### Primary outcome measures

#### Halpern Critical Thinking Assessment (HCTA; [51])

The HCTA involves 25 real-world situations with closed and open questions based on these situations. These situations involve medical research, social policy analysis and other types of problems encountered in everyday life. Five domains of critical thinking are assessed using the HCTA: Verbal reasoning, argument analysis, thinking as hypothesis testing, likelihood and uncertainty, and decision-making and problem-solving. The test includes 5 sets of questions (one open and one closed) for each of these domains. The scoring guide provides answers for forced-choice questions while open-ended questions are graded according to specific grading prompts (for more detail see [61]). Greater scores are awarded to more accurate and comprehensive answers and total scores can range from 0 to 194 [51]. The internal reliability of the HTCA tends to be adequate [51, 61]. The HCTA has been shown to be sensitive to change in previous intervention studies comparing methods of critical thinking instruction [62, 63].

### Heuristics and Biases items [5]

This series of standard items assessing cognitive biases is included as there is evidence that these assess an aspect of critical thinking not captured by traditional measures [5]. These items assess participants’ ability to deal with problems involving causal base rates, noncausal base rates, the law of large numbers, regression to the mean, the gambler’s fallacy, conjunctions, covariation, Bayesian reasoning, framing and probabilistic reasoning (for full details of the items see [5]). Each of these items will be scored as either correct (1) or incorrect (0). Though these are not representative of a unidimensional construct, it has been shown to be useful to aggregate scores on these items [5].

### Five Factor Mindfulness Questionnaire (FFMQ; [52])

This questionnaire assesses levels of dispositional mindfulness. The FFMQ includes 39 items which tap five facts of mindfulness: describing (i.e. labelling experience with words), observing (i.e. paying attention to sensations, thoughts and feelings), non-reactivity (i.e. noticing thoughts without emotionally responding to them), non-judgment (i.e. acceptance of thoughts and feelings) and acting with awareness (i.e. lack of distraction). It employs a 5-point Likert scale (e.g. 1 = never or very rarely true; 5 = very often or always true). This measure has demonstrated adequate internal consistency and construct validity [64].

### Secondary outcome measures

#### Sternberg working memory task [54]

This task is a measure of executive control of working memory. It involves memorising a series of letters and indicating, as quickly and accurately as possible, whether a probe was in this series or not.

### Positive Affect and Negative Affect Schedule (PANAS; [56])

This scale is the most widely-used instrument for assessing inter- and intra-individual differences in experiences of positive and negative emotion. The PANAS-X consists of 60 items. Each item describes a different feeling or emotion and the scale can be used to assess general levels of positive and negative affect by asking participants to indicate to what extent they felt each of these emotions over the past week using a 5-point Likert scale (e.g. 1 = very slightly or not at all; 5 = extremely). Psychometric evaluations tend to find good reliability for the positive and negative subscales [65].

### Warwick-Edinburgh mental wellbeing scale [57]

This is a 14 item scale of mental well-being covering subjective well-being and psychological functioning, in which all items are worded positively and address aspects of positive mental health. The scale is scored by summing responses to each item answered on a 5 point Likert scale. The minimum scale score is 14 and the maximum is 70. A high score reflects a high level of positive mental health and a low score reflects a low level of positive mental health [66].

### Real world outcomes inventory [62]

This is a behavioural checklist focused on life outcomes from many domains ranging in severity from mildly negative (e.g., paying late fees for a movie rental) to severely negative (e.g., spending a night in jail). It was developed based in the Decision Outcomes Inventory [67]. The version employed here is slightly adapted to ensure cultural relevance. Any items which do not fit the Irish context will not be used (e.g. got blisters from sunburn).

### Potential moderators

#### Need for cognition scale [53]

This unidimensional scale measures the extent to which individuals tend to engage in effortful cognitive activity [53]. The scale includes 18 items which are rated on a 5-point Likert scale (e.g. 1 = extremely uncharacteristic of me; 5 = extremely characteristic of me). It has been extensively validated and has been found to have adequate reliability [68].

### Actively open minded thinking scale [8]

This scale assesses the extent to which individuals tend to approach information in an open and flexible manner as opposed to a rigid manner which leads to resistance to belief change. The scale includes 41 items and these are rated on a 6-point Likert scale (e.g. 1 = strongly agree; 6 = strongly disagree).

### Manipulation checks

In week 2 and week 4 participants will complete short questionnaires assessing mindfulness meditation quality and task expectations, enjoyment and difficulty. These will be completed online, allowing participants to complete them at their convenience. Participants will be asked to complete these measures directly following a meditation session.

### Practice quality- mindfulness questionnaire [58]

This 6 item questionnaire assesses perseverance and receptivity during meditation. Perseverance is defined as the ability to continually redirect attention back to the focus of the meditation. Receptivity refers to the willingness to fully experience what is arising during the course of a meditation session. The items are presented alongside a percentage scale and participants are asked to indicate the percentage of time during their meditation session during which their experience reflected each of the item statements. This scale has been shown to fit a 2-factor structure and has demonstrated a predictive relationship between practice quality and improvements in psychological symptoms [58].

### Technology acceptance model questionnaire (TAM; [59])

Items from the TAM assessing expectations, enjoyment and difficulty using the Headspace app will be presented to participants. The TAM is a widely-used measure of user acceptance of technology. The items on this scale are phrased as statements and are measured on a 5-point Likert scale (e.g. 1 = strongly disagree; 5 = strongly agree).

### Intervention acceptability [60]

Four items assessing satisfaction with the intervention were administered. Two questions using a 5 point Likert scale (e.g. 1 = very dissatisfied; 5 = very satisfied) will assess general satisfaction with the programme and satisfaction with the content of the guided sessions in particular. The next two questions require yes/no answers and relate to whether participants would recommend the programme and whether they felt it was worth their time. Questions like these have been used in previous research examining the acceptability of low-intensity online treatments and across a range of different age groups and health conditions [60].

### Statistical analysis

Data will be primarily analysed through a series of 2 × 2 (time – pre, post x group – mindfulness meditation, sham meditation) mixed ANOVAs for each outcome measure using SPSS. The time x group interaction affects will be assessed in order to investigate differences in between the experimental group and the control group in the amount of change on the dependent variables. Correlations between manipulation check measures will also be examined as will their correlations with FFMQ change scores. AMOS will allow simple mediation analyses to be conducted using Structural Equation Modelling (SEM) to test whether executive function, meditation quality and adherence are mediators of any potential relationship between mindfulness and critical thinking. As noted above, these tests will be adequately powered – including SEM analyses (see [69], for evidence of adequate power for simple mediation using SEM in samples as small as *n* = 30). Our analyses will take an intention-to-treat approach and missing data will be treated with a baseline-observation-carried-forward approach. See Table 1 for specific hypotheses.

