	Critical Thinking	Halpern Critical Thinking Assessment^1^, Heuristic and Biases items^2^	2	Critical thinking will increase more for the MM group than for the SM group from t_1_ to t_4_ *(a* ^*1,2*^ *)* and this effect will be moderated by baseline endorsement of thinking dispositions *(b* ^*1,2*^ *)*	Mixed ANOVA, ANCOVA
	Thinking Dispositions	Actively Open-minded Thinking^1^, Need for Cognition^2^	3	Endorsement of critical thinking dispositions will increase more for the MM group than for the SM group from t_1_ to t_4_ *(a* ^*1,2*^ *)*	Mixed ANOVA
	Executive Control	Sternberg Working Memory Task	4	Executive control will increase more for the MM group than for the SM group from t_1_ to t_4_ *(a)* and this increase will mediate the relationship between levels of mindfulness and critical thinking performance following the intervention *(b)*	Mixed ANOVA, SEM
Secondary	Wellbeing	Warwick-Edinburgh Mental Wellbeing Scale	5	Wellbeing will increase and negative affect will decrease more for the MM group than for the SM group from t_1_ to t_4_	Mixed ANOVA
	Positive Affect and Negative Affect	Positive Affect and Negative Affect Schedule subscale	6	Positive affect will increase more for the MM group than for the SM group from t_1_ to t_4_ *(a)*	Mixed ANOVA
	Real-world Outcomes	Real-world Outcomes Inventory	7	Negative real-world outcomes will decrease more for the MM group than for SM group from t_1_ to t_4_	Mixed ANOVA
Manipulation Checks	Meditation Quality	Practice Quality-Meditation	8	Meditation quality will be positively associated with increases in mindfulness *(a)*, executive control *(b)* and critical thinking *(c* ^*1,2*^ *)* and meditation quantity *(d)*, task enjoyment *(e)* and task difficulty *(f)* and it will be higher in the MM group and across time.	Correlation, Mixed ANOVA
	Meditation Quantity	Total Minutes Spent Meditating	9	Meditation quantity will be positively associated with increases in mindfulness *(a)*, executive control *(b)* and critical thinking *(c* ^*1,2*^ *)* and meditation quality *(d)*, task enjoyment *(e)* and task difficulty *(f)* and will not differ across time or groups.	Correlation, Mixed ANOVA

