### Sample size (Incl. flow chart)

The statistical program G*Power was used to conduct power analysis in order to determine the appropriate sample size. Adhering to Cohen’s [48] guidelines for small (*r* = 0.1), medium (*r* = 0.3), and large (*r* = 0.5) effects, two-tailed alpha of .05 was assumed for all tests. With 2 groups, 6 measurements, an assumed correlation among repeated measures of 0.3 (typically low in such research; [49]) as well as a medium effect size (again typical in research on the cognitive effects of mindfulness; [10]) and a power of 0.8, the recommended sample size for mixed (repeated-measures and between factors) ANOVA was 56. As it is recommended that the sample size be a multiple of the number of measurements, a sample of at least 60 will be sought, 30 per group. Because of an anticipated attrition rate of 20 %, 38 participants are required per group i.e. 78 in total. Previous studies using Headspace have reported attrition rates between 20 and 40 % [41, 44]. We expect an attrition rate closer to 20 % because of the incentives in the form of course credit, lunches provided at data collection and free subscription to Headspace for 6 months following the intervention.

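### The primary time-by-group interaction is a change-score test; adjusting for baseline by ANCOVA would be more precise at no cost, markedly so at the assumed correlation of 0.3

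*Protocol article*

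**What the plan says.** The Statistical analysis section states: "Data will be primarily analysed through a series of 2 × 2 (time – pre, post x group – mindfulness meditation, sham meditation) mixed ANOVAs", applied to each outcome measure. The effect of interest is the interaction: "The time x group interaction affects will be assessed in order to investigate differences in between the experimental group and the control group". The section makes clear that what is compared is how far each arm moves from T1 to T4. Table 1 lists mixed ANOVA against every hypothesis about a group effect on a primary or secondary outcome. ANCOVA appears once, in the critical thinking row.

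The Design section places outcome measurement at T1, before randomisation, and at T4, six weeks later. The Sample size section gives "an assumed correlation among repeated measures of 0.3 (typically low in such research", together with a medium effect and "two-tailed alpha of .05 was assumed for all tests". It seeks 30 per group, raised to 38 per group for 20% anticipated attrition, and cites 20 to 40% in earlier studies with the same app. Missing data are to be handled by carrying the baseline observation forward.

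**The concern.** With two arms and two occasions, the interaction compares mean change between arms. A change score subtracts the whole baseline value. When baseline and follow-up are weakly correlated, much of what is subtracted is noise unrelated to follow-up. ANCOVA subtracts only the part of baseline that predicts follow-up, so in a randomised trial it is never less precise, apart from one degree of freedom.

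The protocol itself describes the correlation as low, which is the setting where the change score does worst. The trial is small, and the Discussion already worries that attrition may reduce power. At stake is precision that could be had from data already being collected.

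**Working it through.** **Inputs.** Correlation ρ = 0.3, two-sided α = 0.05, 30 per group analysed, 38 per group randomised and 20% attrition (all Sample size section); T1 before randomisation (Design); mixed ANOVA interaction and baseline carried forward (Statistical analysis). The protocol gives no effect in SD units for the T1 to T4 contrast, so 0.5 SD is my assumption. Equal variances at T1 and T4 are also assumed.

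**The plan's own figure.** The protocol reports "a power of 0.8, the recommended sample size for mixed (repeated-measures and between factors) ANOVA was 56". Taking medium as Cohen's f = 0.25, the between-groups formula λ = f²Nm/(1+(m−1)ρ) with m = 6 measurements and ρ = 0.3 gives N = 56 (power 0.81). The figure therefore reproduces, but as a between-groups effect averaged over six measurements and not as the interaction. That is a separate matter; the comparison below concerns relative precision and does not depend on it.

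**Step 1: the interaction is the change-score test.** For two groups and two occasions, the interaction F equals the square of the two-sample t on T4 − T1. Computing both on one simulated data set gave the same value.

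**Step 2: variance of the arm contrast**, in units of 2σ²/n, complete data, ρ = 0.3:

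- change score: 2(1 − ρ) = 2 × 0.7 = 1.40
- T4 alone: 1.00
- ANCOVA: 1 − ρ² = 1 − 0.09 = 0.91

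Change score against ANCOVA: 1.40/0.91 = 1.54, so 54% more variance and a standard error √1.54 = 1.24 times as large. Against T4 alone: 40% more variance. A simulation with 30 per arm gave 1.48 for the first ratio, which agrees allowing for simulation error and the small cost of estimating the slope.

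**Step 3: power** for 0.5 SD at 30 per arm, complete data, noncentral t: 36% (change score), 48% (T4 alone), 51% (ANCOVA). Sizes for 80% power: 89, 64 and 59 per arm.

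**Step 4: other correlations, complete data.** The ratio simplifies to 2(1 − ρ)/(1 − ρ²) = 2/(1 + ρ), which exceeds 1 for every ρ below 1:

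| ρ | Change score | T4 alone | ANCOVA | Change/ANCOVA |
|---|---|---|---|---|
| 0.3 | 1.40 | 1.00 | 0.91 | 1.54 |
| 0.5 | 1.00 | 1.00 | 0.75 | 1.33 |
| 0.7 | 0.60 | 1.00 | 0.51 | 1.18 |

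**Step 5: the planned carry-forward.** If a fraction a drops out at random and T4 is replaced by T1, the correlation in the analysed data becomes about (1 − a)ρ + a.

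- a = 0.20: 0.8 × 0.3 + 0.2 = 0.44. Change score 2 × 0.56 = 1.12; ANCOVA 1 − 0.44² = 0.81; ratio 2/1.44 = 1.39.
- a = 0.40: 0.6 × 0.3 + 0.4 = 0.58. Change score 2 × 0.42 = 0.84; ANCOVA 1 − 0.58² = 0.66; ratio 2/1.58 = 1.27.

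Carry-forward at 20% also dilutes a 0.5 SD effect to 0.8 × 0.5 = 0.4 SD. Simulated power at 38 per arm with 20% random attrition is about 37% (change score), 40% (T4 alone) and 47% (ANCOVA).

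**The case against.** Four objections deserve an answer.

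*The planned test is sound.* A reader might infer that the mixed ANOVA is biased or invalid. The documents do not support that: T1 precedes 1:1 randomisation, so the interaction estimates the right contrast with the correct type I error, and it matches hypotheses worded as a greater increase from T1 to T4. Chance baseline imbalance affects the estimate in a given sample, but not on average over randomisation. This stands; the issue is efficiency only.

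*The complete-data figures are not the planned analysis.* Carry-forward raises the analysed correlation, so the 54% excess falls to about 39% at the expected attrition. A reader might also take away that the plan is always worse than ignoring baseline. At ρ = 0.3 with complete data that is so, but the gap narrows to 1.12 against 1.00 at 20% attrition and reverses at 40% (0.84 against 1.00). This stands, and the size must be given with those conditions.

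*The value 0.3 is a single planning figure.* It is tempting to say that about a third of the information is lost on every outcome (1 − 0.91/1.40 = 35%). The protocol gives no T1 to T4 correlation for any individual scale, and the questionnaires, reasoning tests and reaction task may well differ. At 0.5 the loss is 25%, and at 0.7 it is 15%. This stands too; the direction does not change, only the amount.

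*The ANCOVA in Table 1.* For the hypothesis that "this effect will be moderated by baseline endorsement of thinking dispositions", a reader might infer that the listed ANCOVA assumes equal slopes and so cannot test moderation. Table 1 names the method and no model terms, and a covariate-by-arm term fits the same framework. That is detail an article may leave to the full plan, and it is not part of this point.

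**Conclusion.** The point holds as a matter of efficiency. The protocol fixes a primary test that is valid but less precise than baseline-adjusted ANCOVA at any pre-post correlation below 1, and its own planning value makes the gap large. The excess variance is 54% at ρ = 0.3 with complete data and about 39% once carry-forward at 20% random attrition is taken into account. In power terms, for an assumed 0.5 SD effect, that is roughly 10 to 15 percentage points.

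These sizes rest on equal variances at the two occasions, dropout at random and the assumed effect. The power figures move with the effect size; the variance ratios do not. If the true correlations are well above 0.3, the gain is smaller but still in the same direction.

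**What to change.** For each outcome measured at T1 and T4, make the primary model the T4 score regressed on arm and the T1 score of the same measure, and report the adjusted arm difference with its 95% confidence interval. The mixed ANOVA may stay as a supporting analysis for readers who want the result expressed as change.

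The cost is an edit to the Statistical analysis section and the analysis column of Table 1, recorded as an amendment in the registry before the condition labels are revealed. No new data, visits or software are needed; the model uses one degree of freedom more.

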### The current study

This protocol paper describes the development of an intervention which makes use of the Headspace mindfulness meditation app for smartphones, tablets and web browsers to evaluate its effects on executive control, critical thinking and key thinking dispositions as well as the real-world outcomes of critical thinking. This intervention was developed in order to test, in the most rigorous way available, hypotheses developed as a result of careful review of the literature on the effects of mindfulness on self-regulation and cognitive abilities and studies carried out previously by the authors suggesting that mindfulness may facilitate more effective critical thinking. The rationale for this intervention relies heavily on a specific type of dual-process theory known as the default-interventionist theory of higher-order cognition [34], which can be used as a framework to integrate research on the effects of mindfulness on attention, executive function and self-regulation of behaviour in general and research on the self-regulation of higher-order cognition, such as critical thinking [17].

In summary, the central research question here is: does regular mindfulness meditation practice facilitate critical thinking through the enhancement of executive function? To answer this, the proposed study aims to ascertain whether a 6-week online mindfulness meditation intervention increases trait mindfulness, executive function, critical thinking performance and endorsement of key critical thinking dispositions to a greater extent than an active-control sham meditation condition. The hypotheses to be tested can be seen in Table 1. This aim will be achieved by testing these hypotheses using the measures and analyses described in the next section. It is also intended to investigate the role of executive function in mediating the predicted positive relationship between mindfulness and critical thinking performance. Finally, the study aims to explore the participants’ experiences of taking part in an online mindfulness meditation intervention and the real-world outcomes they perceived.

**Table 1 Tab1:** Study hypotheses

Outcomes	Variable	Measure		Hypothesis	Analysis
Primary	Mindfulness	Five Facet Mindfulness Questionnaire	1	Mindfulness will increase more for the mindfulness meditation (MM) group than for the sham meditation (SM) group from t_1_ to t_4_	Mixed ANOVA

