	Task Enjoyment	Technology Acceptance Model Questionnaire subscale	10	Task enjoyment will be positively associated with increases in mindfulness *(a)*, executive control *(b)* and critical thinking *(c 1,2*) and meditation quality *(d)*, meditation quantity *(e)* and task difficulty *(f)* and will not differ across time or groups.	Correlation, Mixed ANOVA
	Task Difficulty	Technology Acceptance Model Questionnaire subscale	11	Task difficulty will be positively associated with increases in mindfulness *(a)*, executive control *(b)* and critical thinking *(c 1,2*) and meditation quality *(d)*, meditation quantity *(e)* and task difficulty *(f)* and will not differ across time or groups.	Correlation, Mixed ANOVA
	Intervention Acceptability	Items from Kirkpatrick et al. [60]	12	Intervention acceptability will be positively associated with increases in mindfulness *(a)*, executive control *(b)* and critical thinking *(c* ^*1,2*^ *)* and meditation quantity *(d)*, task enjoyment *(e)* and task difficulty *(f)* and it will be higher in the MM group but will not differ across time.	Correlation, Mixed ANOVA
	Attrition	No. of participants lost from baseline to t_4_	13	Attrition will be negatively associated with meditation quality *(a)*, meditation quantity *(b),* task enjoyment *(c)* and task difficulty *(d)* and will not differ across time or groups.	Correlation, Mixed ANOVA

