There are however some weaknesses associated with this study also. While every effort was made to ensure that the only difference between the guided mindfulness meditations and the guided sham meditations would be the provision of specific instructions to do with building specific mindfulness skills in the experimental condition, it could be that this manipulation makes these guided sessions more engaging and enjoyable than the guided sham meditations. This could lead to differences in attrition rates across the two conditions. Attrition rates in general could be larger than expected which may affect the statistical power of the analyses. Finally, participants will be drawn from the student population only and so any conclusions made based on this study may not be generalizable to the wider population. However, critical thinking is a skill which is of particular importance as an outcome of university education and therefore this study may have practical benefits.

Many companies, universities and other institutions are introducing mindfulness programmes with the promise of improving thinking skills [72]. While there are theoretical and historical reasons supporting this view, it has not been adequately investigated. The significance of this study lies in its rigorous approach to investigating this claim for the first time in the context of an RCT.

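### Correlations of meditation quality and acceptability with gains (H8a-c, H12a-c) carry no term for arm, although the plan predicts both sides to be higher in the mindfulness arm

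*Protocol article*

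**What the plan says.** The Statistical analysis section of the protocol article plans a time-by-group mixed ANOVA for each outcome and names group explicitly there. For the manipulation checks it says only: "Correlations between manipulation check measures will also be examined as will their correlations with FFMQ change scores".

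Table 1 (under The current study) lists Correlation and Mixed ANOVA as the methods for these checks and widens the correlations to gains in executive control and critical thinking:

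- **H8:** "Meditation quality will be positively associated with increases in mindfulness", and likewise with the other two gains. The same row predicts of meditation quality that "it will be higher in the MM group and across time".
- **H12:** the same associations are predicted for intervention acceptability, and of its level the row says "it will be higher in the MM group but will not differ across time".
- **H1:** "Mindfulness will increase more for the mindfulness meditation (MM) group than for the sham meditation (SM) group". H2a and H4a make the same prediction for critical thinking and executive control.
- **H9 to H11** (meditation quantity, task enjoyment, task difficulty): associations with the gains are predicted, but each row ends "and will not differ across time or groups".

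No partial correlation, within-arm analysis or arm covariate is named for any correlation. Pooling over arms is not stated either.

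**The concern.** H8a-c and H12a-c are there to show that participants who practised better, or who found the programme more acceptable, gained more. If the plan's own arm predictions are right, random allocation raises both the check measure and the gain. Ignoring arm then yields a positive correlation even if, inside each arm, quality has nothing to do with gain.

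Success on H1 and on the arm contrast in H8 would thus push H8a towards significance by itself. A reader would take as separate evidence about practice quality something that partly repeats the randomised comparison. Eight planned tests are exposed: two checks, each against mindfulness, executive control and the two critical thinking measures (2 × 4 = 8).

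**Working it through.** **The plan's own figure.** The protocol gives no sample size, effect size or power for the correlations. Its only calculation is N = 56 for the mixed ANOVA (Sample size section). That reproduces with the between-factors formula, f = 0.25, six measurements and a correlation of 0.3:

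- λ = N·f²·m / (1 + (m − 1)ρ) = 56 × 0.0625 × 6 / (1 + 5 × 0.3) = 21 / 2.5 = 8.4, giving power 0.812.

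The figure matters here only for what the plan's effect size can be taken to mean (see the objection).

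**Inputs.**

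- From the protocol: 30 per arm (N = 60), 1:1 allocation, two-sided alpha 0.05.
- Assumed: the arm differences on the check and on the gain, in within-arm SD units, because none is given for quality or acceptability. The range is 0.5 SD (medium on the d scale, d = 2f with f = 0.25), 0.63 SD (the section's medium r = 0.3, since d = 2r/√(1 − r²) = 0.6/0.954 = 0.63) and 0.8 SD.
- Assumed: normal data and zero correlation inside each arm.

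**Correlation induced by arm alone.** With equal arms, arm adds d²/4 to each variance and d₁d₂/4 to the covariance, so

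r = d₁d₂ / √[(d₁² + 4)(d₂² + 4)].

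With equal differences on both sides this becomes d²/(d² + 4):

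- 0.5 SD: 0.25 / 4.25 = 0.06
- 0.63 SD: 0.396 / 4.396 = 0.09
- 0.8 SD: 0.64 / 4.64 = 0.14

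**Rejection rates** (40,000 simulated trials per scenario, N = 60, two-sided 5%, no within-arm association):

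| Difference on check / gain (SD) | Induced r | Pooled test | Partial correlation given arm |
|---|---|---|---|
| 0 / 0.5 | 0.00 | 5.0% | 5.1% |
| 0.5 / 0.5 | 0.06 | 7.2% | 4.8% |
| 0.63 / 0.63 | 0.09 | 10.3% | 5.1% |
| 0.8 / 0.5 | 0.09 | 10.6% | 5.0% |
| 0.8 / 0.8 | 0.14 | 18.4% | 5.1% |

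The excess lies in the predicted, positive direction: at 0.8 / 0.8, 18.3 of the 18.4 percentage points are positive rejections. At N = 78 the pooled rates for the three equal-difference rows are 8.1%, 12.3% and 22.9%.

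**Which pairs are affected.** The first row shows that a check with no arm difference has no problem. Under the plan's own predictions that covers quantity, enjoyment and difficulty (H9 to H11). Among the check-by-check correlations, Table 1 pairs quality and acceptability only with measures predicted not to differ by arm, so no listed pair has a predicted difference on both sides. H8a-c and H12a-c remain.

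**The case against.** **Silence is not a choice.** The article does not say that the arms are pooled, and a separate analysis plan could add a term. This stands in part: pooling is implied only. But the article names a method for each hypothesis, and it writes group into the ANOVAs while naming a bare correlation here. Carried out as written, the analysis is a plain correlation.

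**The rejections are errors only against a within-arm null.** H8 and H12 speak of a positive association. If arm raises both variables, the overall association really is non-zero, and rejecting is correct in that literal sense. This stands as a limit on wording: the 7% to 18% are error rates for the claim that quality matters beyond arm. It does not rescue the analysis, since an association produced by arm alone says nothing about practice quality beyond the arm effect. Nor does the plan to test quality as a mediator: if quality drives gain, the two remain related inside the arms, where the adjusted test can find it.

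**Broader scope.** A reader might infer that all manipulation-check correlations are compromised, including the relation of amount of practice to gain. The documents do not support that: total minutes, enjoyment and difficulty are predicted equal across arms. The one hint the other way is the Discussion's concession that "it could be that this manipulation makes these guided sessions more engaging and enjoyable than the guided sham meditations".

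**Larger size.** A reader might convert f = 0.25 into 0.85 SD of change (√(4 × 0.0625 × 2 / 0.7)), pair it with a 1.0 SD difference in quality and arrive at a rejection rate of 27%. Neither input is supported. The 1.0 SD is nowhere in the protocol, and the conversion treats f as a time-by-group interaction effect, whereas 56 comes from the between-factors formula (the interaction formula gives 26 with six measurements, or 46 with two). Nor does arm alone usually give significance: the critical correlation at N = 60 is 0.254, reached on average only at about 1.17 SD on both sides.

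**Low consequence.** These are supporting analyses, and the ANOVAs planned for the same checks will show any arm difference alongside. True, and it limits the weight of the point.

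**Conclusion.** The point holds for H8a-c and H12a-c. As written, these eight tests mix the randomised arm contrast with any association inside the arms, and the plan's own predictions make both sides differ by arm in the same direction. With assumed differences of 0.5 to 0.8 SD on both sides, N = 60, normal data and no within-arm association, the induced correlation is modest and the rejection rate is roughly one and a half to three and a half times nominal. If the true difference in quality or acceptability is near zero, there is no inflation.

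This is an inexpensive improvement to supporting analyses and no threat to the trial's efficacy conclusions.

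**What to change.** For H8a-c and H12a-c, state that the test is the partial correlation given arm (equivalently, a regression of the change score on the check measure plus arm). Show the correlation within each arm beside it, and label the pooled correlation as descriptive only.

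Using the same adjustment for H9 to H11 is a harmless precaution, since an arm difference in enjoyment is conceded as possible.

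The cost is one sentence and one degree of freedom per test. Blinding is preserved: the Condition A and Condition B labels described under Recruitment and randomisation are enough to fit the arm term before the conditions are revealed. No new data and no change to the primary ANOVAs are needed.
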